### **b. Modification or interruption of the intervention**

During the implementation of this study, the intervention will be interrupted for each participant who presents (12):

- Withdrawal of informed consent;
- Discontinuation of treatment;
- Lost view ;
- Failure to process.

Chart 3 : Criteria for leaving the study outside of the cure

| Criteria                                        | Definition                                                                                                                                                       |
|-------------------------------------------------|------------------------------------------------------------------------------------------------------------------------------------------------------------------|
| Abandonment-confirmed                           | Patient absent for two consecutive weeks (declared abandonment in the third) sought by the RECOs and confirmed as having abandoned                               |
| Unconfirmed abandonment                         | Patient absent for two consecutive weeks (declared abandonment in the third) but his actual method of discharge (abandonment or death) not having been confirmed |
| Death                                           | Participant whose death has been certified by a nursing staff                                                                                                    |
| Lost view                                       | Change of address, followed in another CS outside the study area                                                                                                 |
| Treatment failure                               | Referred to UNTI following the appearance of danger signs (temporary discharge *)                                                                                |
| Withdrawal of consent                           | Any time after randomization                                                                                                                                     |
| Non-response to treatment (even if very rarely) | Children who do not recover after 12 weeks of treatment                                                                                                          |

*\*AT their return the children of the arm with reduced dose will resume with the dose planned for the week in which they were transferred, so they do not restart the treatment from zero but continue it.*

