### c. Strategies to improve protocol adherence

Every evening, the principal investigator, the ACF Research RP and the three data collectors check all the data collected in the field in the different UNTAs. Inconsistencies, outliers or missing information for certain variables are noted and communicated to ACF supervisors who follow up within 24 hours and strengthen the capacities of UNTA agents, and also to RECOs. During their visit to enter data, data entry clerks also communicate certain weaknesses observed to healthcare providers with a view to correcting the data as far as possible.

In some cases where trained providers have moved or left their posts, other providers will be trained by the research team to ensure the continuity of the study.

For each child who does not respond to an appointment, RECO makes a home visit to find out what is going on.

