##### b. Additional results

The additional results expected in this study, in the two groups (control and intervention), are:

- **The duration of the edema melting:** calculated in number of days, this indicator corresponds to the time taken for the lower limbs of SAM children to return to their normal volume. The expected result is the onset of melting of the edemas within the first 14 days after admission and their complete disappearance after 21 days of treatment.
- **The length of stay:** calculated in number of days, this indicator corresponds to the time elapsed between admission and discharge ( $PB \geq 12.5\text{cm}$  and / or  $PT \geq -3$  Z score and / or edema melt). The maximum length of stay is 12 weeks or 3 months(12).
- **The cure rate:** A child will be considered cured if he meets the cure criteria according to his admission category: A  $PT \text{ index} \geq -1.5$  or  $PB \geq 125 \text{ mm}$  during two consecutive visits and no edema during two visits (2 consecutive weeks).
- **The dropout rate:** it is the proportion of children confirmed alive who missed two successive visits. The abandonment is confirmed once after the visit of the RECO which confirms that the child is alive despite his 2 absences during the weekly visits. Children who have abandoned will be followed up to 3 months after the abandonment. For children who can be found, offer the caregivers a small snack at the single appointment 3 months after abandonment to take the anthropometric measurements.
- **Death rate :** the proportion of children randomized to the study who died during the intervention at any time.
- **Cost savings** (average cost saved and cost saved per child treated): this involves comparing the cost of treatment for children in care and declared cured in the two groups. We will use a societal perspective including the direct costs of drugs and RUTF

(purchase, transport, transport and storage) to assess the cost for each child, the HR costs involved in the care, the non-medical costs (food and transport. beneficiaries), indirect costs (loss of productivity).

- The growth velocity of the anthropometric variables and indices: it will be a question of evaluating the prevalence of stunting, underweight of the children included in the study in the two groups at the end of the treatment.

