| Evaluate the duration of treatment for each participant in the two groups                    | Duration of the treatment                    | Time between admission and discharge (PB≥12.5cm or PT ≥-3 Z score or edema melt)                                                                                                         | number of days           | interval |
| Assess dropout, cure, treatment failure and mortality rates                                  | Dropout rate in each arm                     | Number of children who have abandoned treatment and who no longer come to the center even after 3 home visits / total of children followed in each arm                                   | percentage               | interval |
|                                                                                              | Recovery rate                                | Percentage of children having reached the discharge after 3 months of treatment                                                                                                          | percentage               | interval |
|                                                                                              | Proportion Transfer to hospital in each arm  | Number of children being transferred to hospital during treatment (3 months) following a medical complication or if stagnation or loss of appetite / total children followed in each arm | percentage               | interval |
|                                                                                              | Proportion of Deaths in each arm             | Number of children who died during the stay at UNTA or during transfer to UNTI / total child followed in each arm                                                                        | percentage               | interval |
| Evaluate the cost and savings made with a reduced dose of RUTF compared to the standard dose | % savings in SAM treatment with reduced dose | Difference in cost between treatment with standard dose and treatment with reduced dose, expressed in%                                                                                   | percentage               | interval |

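### The dropout rate is defined incompatibly in section 2.1.4 b and Annex 8, and under section 2.1.4 b unconfirmed abandonment falls in no performance indicator

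*Protocol*

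**What the plan says.** Three places in the protocol bear on who is a dropout.

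- **Section 2.1.4 b (Additional results)** defines the outcome: "it is the proportion of children confirmed alive who missed two successive visits". It adds: "The abandonment is confirmed once after the visit of the RECO which confirms that the child is alive despite his 2 absences". It names no denominator.
- **Annex 8 (list of variables)** defines the dropout rate in each arm as: "Number of children who have abandoned treatment and who no longer come to the center even after 3 home visits". It divides by the "total of children followed in each arm". It sets no condition on vital status.
- **Section 2.1.3 b, Chart 3** lists exits from the study other than cure. Confirmed abandonment is: "Patient absent for two consecutive weeks (declared abandonment in the third) sought by the RECOs and confirmed as having abandoned". Unconfirmed abandonment has the same absence, but with "his actual method of discharge (abandonment or death) not having been confirmed".

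The secondary objectives in section 1.2 list the performance indicators as cure, dropout, mortality, non-response and transfer to hospital. The secondary hypotheses expect equal performance in the two arms and name dropout and death among the indicators. Section 2.3.3 analyses secondary results by intention to treat only. Nothing says which definition of dropout produces the reported rate.

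**The concern.** A rate that is compared between arms needs one numerator and one denominator. Here the outcome section and the variable list disagree on the trigger, on vital status and on the denominator, so two analysts could follow the protocol and report different rates from the same records.

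The condition that the child be confirmed alive matters most. A family that cannot be traced is the case in which a death is most easily missed, and section 2.1.4 b leaves that child out of the dropout rate. If untraced departures are more common in one arm, that arm's dropout rate is lowered by the definition itself. The comparison could then support similar performance, or favour the arm with poorer follow-up, for a reason unrelated to how many children left treatment.

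**Working it through.** **1. The definitions side by side**

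| | Section 2.1.4 b | Chart 3 | Annex 8 |
|---|---|---|---|
| Trigger | two successive missed visits | two weeks' absence, recorded in the third | not attending after three home visits |
| Vital status | must be found alive | split into confirmed and unconfirmed | no condition |
| Denominator | not stated | none (exit classes, not a rate) | children followed in the arm; followed is not defined |

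**2. Two test children**

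- Child A misses two visits, is found alive at one relay visit, and returns before a third home visit. This is a dropout under section 2.1.4 b but not under Annex 8.
- Child B misses two visits and is never found, despite three home visits. This is not a dropout under section 2.1.4 b, because the child is not confirmed alive. Annex 8 can count it. Chart 3 files it as unconfirmed abandonment.

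**3. Child B against each performance indicator, using section 2.1.4 b for dropout**

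- Cure: no, the criteria were never recorded as met.
- Dropout: no, not confirmed alive.
- Mortality: no, Chart 3 requires that nursing staff certify the death.
- Non-response: no, Chart 3 requires failure to recover after 12 weeks of treatment.
- Transfer: no, unless an earlier transfer had already been counted.

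Chart 3's lost-to-view class does not help either, since it covers a change of address or care at a centre outside the study area. Child B thus has an exit category but is an event in none of the indicators.

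**4. Illustration of size**

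The protocol gives no figure for the share of untraced children, so the rates here are assumptions. Inputs:

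- 500 children per arm (Annex 5);
- 20% abandon (assumed; the value equals the planning allowance in section 2.1.6 but is used only as a round number);
- a share *u* of those who abandon is untraced (assumed, 0% to 50%).

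Abandonments per arm: 0.20 × 500 = 100. Rate under section 2.1.4 b, taking all randomised children as denominator: 100 × (1 − *u*) / 500.

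| *u* | Section 2.1.4 b rate | In no indicator | Confirmed plus unconfirmed |
|---|---|---|---|
| 0% | 100/500 = 20% | 0 (0%) | 20% |
| 10% | 90/500 = 18% | 10 (2%) | 20% |
| 25% | 75/500 = 15% | 25 (5%) | 20% |
| 50% | 50/500 = 10% | 50 (10%) | 20% |

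Between arms: let both arms truly lose 20%, with *u* = 25% in the control arm and 50% in the reduced-dose arm. The reported rates are 15% and 10%, a difference of 5 percentage points where none exists.

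For Annex 8, let a share *r* of the 100 return before a third home visit (assumed 0%, 20%, 40%) and count untraced children. The rate is 100 × (1 − *r*) / 500 = 20%, 16% or 12%. Over the assumed ranges of *u* and *r*, the reported rate runs from 10% to 20%, depending on the definition used.

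**The case against.** The best defence is that the conflict is narrow. Chart 3 and section 2.1.4 b agree on a two-week absence with a relay's confirmation, and the mention of the third week says when the absence is recorded, not that the threshold differs. The outlier on the trigger is one row of an annex. That stands, but the row is the protocol's variable definition for the rate, and it also differs on vital status and denominator.

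It can also be said that a sensitivity analysis belongs in the statistical analysis plan, which is not at hand. That stands too: its absence is not criticised here. The contradiction between definitions lies in the protocol itself.

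Four stronger readings are tempting and are not supported.

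- **Untraced children have no exit category.** They do: Chart 3's unconfirmed abandonment. What they lack is a performance indicator under section 2.1.4 b. Annex 8 can count them.
- **The two triggers give rates that differ many-fold.** This equates three home visits with three missed weeks. Section 2.1.3 c says only: "For each child who does not respond to an appointment, RECO makes a home visit". It fixes no interval between visits and no limit on their number. A large multiple also needs absences to be independent from week to week, whereas abandonment persists. If, for illustration, permanent departure is equally likely before each of 8 visits, 7/8 of leavers miss at least two visits and 6/8 at least three, a ratio of (7/8)/(6/8) = 1.17.
- **The conflict changes who receives RUTF.** Interruption of the intervention is set out in section 2.1.3 b. Section 2.1.4 b and Annex 8 define outcome rates, and no contradictory rule on interruption is shown.
- **The conflict undermines the 20% allowance in the sample size.** The formula in section 2.1.6 with its rounded z values gives (1.64 + 0.84)² × 2 × 2.6² / 0.5² = 332.6 per group, and unrounded z values give the stated 335. The 1,000 children planned leave 2 × 335 = 670 even after 33% loss.

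**Conclusion.** The concern holds as a contradiction in the definition of a secondary outcome that carries a stated hypothesis. That the definitions are incompatible follows from the text alone and needs no assumption. So does the finding that, if section 2.1.4 b is applied as written, children with unconfirmed abandonment are events in no performance indicator.

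The size is illustrative. It depends on the assumed 20% abandonment and the assumed shares untraced or returning, none of which the protocol gives. A bias between arms arises only if the share untraced differs by arm, which cannot be known in advance. The primary outcome definition and the sample size do not depend on this point.

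**What to change.** - Reconcile section 2.1.4 b, Chart 3 and Annex 8 to one outcome definition of dropout, with all randomised children in the arm as denominator. The death rate in section 2.1.4 b already refers to randomised children.
- Report confirmed and unconfirmed abandonment separately, and their sum as the dropout rate, using the classes in Chart 3.
- Add a sensitivity analysis that counts unconfirmed cases as deaths. It may sit in the protocol or in the statistical analysis plan.
- Make the absence count, the number of home visits and any wording on interrupting treatment agree across these places. Which rule to adopt is for the investigators; this review proposes none.

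The cost is protocol wording and one results table. Chart 3 already distinguishes the classes, so no new data item is needed.

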#### **4) Secondary outcomes**

- **Acceptance** of a reduced dose during SAM treatment by healthcare staff as well as the community: this involves assessing the perceptions of families and healthcare providers on the amount of RUTF received, consumption practices and 'uses and their attitude to dose reduction.
- **The relapse rate:** this is the proportion of children in care for SAM and declared cured who become SAM again in the 3 months after the end of treatment.
- **Psychomotor development :** This sub-study aims to assess the proportion of children with psychomotor developmental delay (DPM) and to monitor their progress during treatment. Psychomotor Developmental Delay (RDPM) is understood to mean disorders in the acquisition of skills and competences in the areas of language, cognitive, motor and social interaction. The RDPM corresponds to a score of less than 70% in two of the four domains of the DPM(34). For this sub-study, it is expected that the MPD of children with RDPM will improve after their management.(35) (36) (37) due to the simple fact of the medical and nutritional intervention without particular action on the DPM during the treatment.

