The effects of malnutrition on psychomotor development depend on the stage and nature of the deficiency concerned. (12). Malnutrition is responsible for the functional isolation that causes RDPM by reducing social interactions, exploratory behavior, attention, motivation and a low level of activity(13) (14) (15). Functional isolation and its consequences will be all the more serious if it is the mother-child relationship (or the mothering environment, if applicable) that is disrupted.(17) (18). In addition, severe acute malnutrition has been shown to cause permanent anatomical and biochemical changes affecting brain development. Children with SAM reportedly have reduced brain size and EEG abnormalities(19) (20). More recently, researchers have shown that children with SAM have more pronounced RDPM in certain areas.(21). The consequences of SAM in early childhood would be felt for very long periods, sometimes throughout life, rendering victims incapable of being independent in

adulthood.(22). This RDPM would be reduced if children benefit from good nutritional care(23). If the care is provided correctly, the beneficial effects on psychomotor development are felt very quickly: on motor development in the 24 months following the treatment. The development quotient would improve from the second year(24) (25).

Often malnutrition occurs in a context of poverty where parents are unable to provide children with all the care and conditions necessary for their development in terms of DPM. To be reassured that the observed RDPM is due to malnutrition, it is necessary to go through the randomization of the participants. In addition, it is necessary to study together the other associated factors, including the psycho-emotional environment from which the child with SAM evolves.

This is the reason why this study is proposed in order to determine the prevalence of RDPM in SAM children and to assess their evolution after treatment in the ZS of Nzaba and Bonzola in the province of Kasai Oriental in the DRC.

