### 3.1.4. Sample size

$$n = t^2 \times p \times (1-p) / m^2$$

- *n: Minimum sample size to obtain significant results for an event and a fixed level of risk*
- *t: Confidence level (the typical value of the 95% confidence level will be 1.96)*
- *p: estimated proportion of the population exhibiting the characteristic studied (0.50 is considered if p is unknown);*
- *m: Margin of error (generally set at 5%).*

Applying the above formula, the minimum sample for this study is 384 children. After rounding up, a total of 400 children will be included in the study on psychomotor development, including 200 in the intervention group (reduced dose) and 200 in the control group (standard dose).

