##### **Duration and pace of the assessment**

For each participant, the test lasts between 10 to 15 minutes maximum. Each child will undergo three assessments, one on admission, one at discharge in the third month (exit from treatment for children declared cured) and one in the sixth month.

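### The psychomotor sub-study credits treatment with improvement in children picked for a low admission score, although every child is treated and part of that improvement is regression to the mean

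*Protocol*

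**What the plan says.** Section 2.1.4, under Secondary outcomes, defines delay by a cut-off: "The RDPM corresponds to a score of less than 70% in two of the four domains of the DPM". It then states that "it is expected that the MPD of children with RDPM will improve after their management" (MPD is evidently DPM, psychomotor development) and gives the cause as "due to the simple fact of the medical and nutritional intervention without particular action on the DPM during the treatment".

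Annex 3 (Duration and pace of the assessment) schedules three tests: "one on admission, one at discharge in the third month (exit from treatment for children declared cured) and one in the sixth month". There is one admission test and no repeat baseline. Annex 3, Section 3.1.4, takes 400 children, 200 per arm. Under Section 2.1.3 both arms receive RUTF and the care of the national protocol, and differ only in RUTF dose from week 3.

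The Annex 3 rationale adds: "To be reassured that the observed RDPM is due to malnutrition, it is necessary to go through the randomization of the participants".

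The planned inference is between arms. The secondary hypothesis is equal psychomotor development in the two dose groups. Annex 3, Section 3.1.3, describes evolution according to RUTF dose, and Section 3.3.2 names a chi-square test and a t-test between the two groups.

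**The concern.** Children enter the delayed group because they scored low on one test, and the same test is then repeated. If the test has any measurement error, some low admission scores were low by chance, and the group drifts upward on retest with no change in any child. On delay status the group starts at 100% delayed, so its share can only stay or fall.

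Nothing in the design separates this drift, or anything else that happens over the same months, from an effect of treatment. All sampled children have SAM and all are treated. Annex 8 mentions well-nourished children, but no section recruits or tests such a group.

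The randomisation sentence in Annex 3 has a related fault. The trial randomises RUTF dose. It does not randomise malnutrition, or treatment against none, so it cannot show that delay is due to malnutrition.

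At stake is a separate article on psychomotor development, listed in the activity timetable. Written to the outcome text as it stands, it would report an uncontrolled change in a selected group as a benefit of treatment.

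**Working it through.** **The plan's own figure.** Annex 3, Section 3.1.4: n = t² × p × (1 − p) / m², with t = 1.96, m = 0.05 and p = 0.5 ("0.50 is considered if p is unknown"). This gives 3.8416 × 0.25 / 0.0025 = 384.16, which reproduces the stated 384, rounded up to 400. That figure is not in dispute.

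**Inputs for the check.**
- From the protocol: 400 children, four domains, delay defined on two of four domains (read as at least two), one admission test.
- Prevalence of delay at the cut-off is not given. Range used: 4.5% (between the 4.1 and 4.9 for severe delay cited in the Annex 3 rationale, read as percentages) to 50% (the planning p).
- Assumed, because the protocol gives neither: test-retest reliability r from 0.6 to 0.95, and a correlation of 0.5 between the true domain scores.

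**Model, with no true change in any child.** For each domain, score = √r × true score + √(1 − r) × error, with a fresh error at each test. The cut-off is set to give the chosen prevalence at admission. Children below it in at least two domains are followed to the second test.

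**Results at r = 0.8:**

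| Delayed at admission | Number of 400 | No longer delayed | Mean rise in delayed group | Chance the group mean rises |
|---|---|---|---|---|
| 4.5% | 18 | 48% (about 9) | 0.138 SD | 0.960 |
| 10% | 40 | 40% (16) | 0.111 SD | 0.986 |
| 25% | 100 | 29% (29) | 0.081 SD | 0.997 |
| 50% | 200 | 19% (38) | 0.052 SD | 0.992 |

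The mean change in all sampled children is 0.00 SD.

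**Check by formula.** The mean of the four domains has true variance 0.8 × (1 + 3 × 0.5) / 4 = 0.50 and error variance 0.2 / 4 = 0.05. On retest a selected group regains 0.05 / 0.55 = 9.1% of its shortfall. A rise of 0.138 SD then implies an average shortfall of 0.138 / 0.091 = 1.5 SD, and a rise of 0.052 SD implies 0.6 SD. Both are plausible for the rarest and the commonest delay group.

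**Other reliabilities.** Over r = 0.6 to 0.95, 10% to 63% stop being classed as delayed and the mean rise is 0.01 to 0.28 SD. The chance that the group mean rises is 0.89 to 0.97 at r = 0.9 and 0.79 to 0.91 at r = 0.95.

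**The reverse flow.** With no true change, the expected number delayed is the same at both tests. At 25%, 29 of the 100 delayed children leave the category, so 29 of the other 300 are expected to enter it. Following only the delayed children hides the second number.

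**The randomised comparison.** With no difference between arms, at r = 0.8 and 25% delayed, a t-test on change between arms within the delayed children rejected in 5.25% of 2,000 simulated trials. Regression to the mean acts equally in both arms.

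**The case against.** The strongest reply is that the protocol states an expectation, with literature citations, and not an analysis or a decision rule. The formal hypothesis, the stated tests and the evolution result in Annex 3, Section 3.1.3, all compare arms. The evolution objective in Annex 3, Section 2, covers all SAM children, where this artefact is absent. Any within-group method could sit in a statistical analysis plan that is not shown. The Annex 3 sentence on randomisation is background, and the text after it says that other associated factors must be studied too.

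Most of this stands, and it limits the point. No paired test in delayed children is planned, so false-positive rates for such a test are only illustrative: 0.13 to 0.22 at reliability 0.95, 0.18 to 0.42 at 0.9 and 0.39 to 0.72 at 0.8. A reader might infer that a favourable conclusion follows almost whatever happens. The documents do not support that. The size depends on a reliability they do not give, only the no-change case was examined, and scores, unlike the category, can fall: a true decline larger than the artefact would lower the group mean.

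The reply does not rescue the causal wording. An outcome definition fixes the group, the expected direction and the cause, and the design cannot support that cause under any later choice of test.

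**Conclusion.** The point holds as a fault of attribution. Improvement in children classed as delayed on a single admission test cannot be credited to treatment, because all are treated and the group is selected on a low score. At an assumed reliability of 0.8 and a prevalence of 4.5% to 50%, regression to the mean alone would move 19% to 48% of them out of the delayed category and raise their mean by 0.05 to 0.14 SD. These sizes also rest on the assumed inter-domain correlation of 0.5. That the attribution is unsupported rests on no assumption, and neither does the error about what randomisation can show.

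A reader might also infer that the trial's psychomotor comparison or its main result is compromised. Neither is: regression to the mean does not bias the comparison of arms, and the primary outcome, weight gain velocity, does not use these scores. The text should be changed, but this is a secondary sub-study and the trial's main conclusion does not depend on it.

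**What to change.** In Section 2.1.4, psychomotor development outcome, delete the attribution to the medical and nutritional intervention and state instead that:
- change in domain scores from admission to discharge and to month 6 is described in all sampled children with an assessment, noting that the discharge assessment covers only children declared cured;
- delay status is shown as a full two-way table, including children not delayed at admission who become delayed;
- treatment-effect conclusions come only from the randomised comparison of arms, adjusted for the admission score.

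In the Annex 3 rationale, delete or correct the sentence on randomisation and malnutrition, since only RUTF dose is randomised.

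The cost is wording in two places and one table. No new data are needed, because the assessments are already scheduled for all sampled children and not only for those with delay. The sub-study gives up a causal before-after claim that its design cannot support.
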